## Abstract

**Background:**

In typically developing children, participation in sports has been proven to be positively correlated to both physical and psychosocial health outcomes. In children and adolescents with a physical disability or chronic disease participation in both recreational and competitive sports is often reduced, while for this population an active lifestyle may be even more important in reaching optimal levels of physical and psychosocial health. Therefore, the aim of the Health in Adapted Youth Sports (HAYS) Study is to determine both negative and positive effects of sports on children and adolescents with a chronic disease or physical disability.

**Methods:**

In this cross-sectional study differences will be compared in regards to physical and psychosocial health, cognitive functioning, school performance, daily physical activity and injuries between children and adolescents with a chronic disease or physical disability who participate in sports and those who do not. Children and adolescents, both ambulatory and wheelchair dependent, in the age of 10–19 years with a physical disability or chronic disease will be included. “Sports” is defined as participation in an organized sport at least two times a week for a duration of 3 months or more prior to the assessment. Parametric and non-parametric statistics will be used to determine the differences between the two groups.

**Discussion:**

This study provides insight in the effects of sports participation in relation to health, psychosocial functioning, physical activity and school performance in children and adolescents (10–19 years) with a chronic disease or physical disability. Results will guide healthcare professionals working with these children to better guide this population in reaching optimal levels of health and physical activity levels.

## Background

Children with disabilities often show reduced fitness levels and physical activity patterns and they participate less in competitive and recreational sports compared to their non-disabled peers (Murphy and Carbone 2008; van Brussel et al. 2011). The relationship between health and physical fitness has been studied by many authors.

In the general population, low level of physical activity is highly associated with low physical fitness, an increased cardiovascular and overall mortality (Arraiz et al. 1992; Blair et al. 1989; Colditz et al. 2002; Erikssen 2001). In typically developing children, participation in sports has been proven to be positively correlated to both physical and psychosocial health outcomes (Eime et al. 2013). Also for adults with various disabilities the physical, psychological, social, and economic benefits of participation in sports and recreational activities are described previously (Richter et al. 1996; Klapwijk 1987; Jackson and Davis 1983; Hutzter and Bar-Eli 1993). Because of the reduced fitness levels and physical activity pattern in children with a disability or chronic disease, support for an active lifestyle, including participation in sports, may be even more important in this population.

Next to the possible benefits of sports on health and fitness level, increasing evidence also shows benefits from physical activity on school performance and level of cognition could be influenced in a positive way. Children and adolescents without a medical condition are already known to perform better at school when being physically active (Basch 2011; Donnelly et al. 2009; Sallis et al. 1999; Singh et al. 2012). Childhood physical fitness is also associated with higher levels of cognition and appeared to be a good predictor of school performance and level of cognition 1 year later (Chaddock et al. 2011; Pontifex et al. 2012; Tomporowski et al. 2008; Chaddock et al. 2012; London and Castrechini 2011).

Participation in sports could also have an positive influence on health related quality of life (HRQoL) and self-worth (Eime et al. 2013). HRQoL refers to the impact of health and illness on an individual’s quality of life. In relation to sports, adult athletes with cerebral palsy for example reported a positive influence of sports participation on their HRQoL (Groff et al. 2009; Verschuren et al. 2007).

When looking at competence levels, Special Olympics participants with developmental disorders showed higher levels of self-worth and perceived physical competence in comparison to nonparticipants (Weiss et al. 2003). These findings might support the hypothesis that sports participation will enlarge the global self-worth of children and adolescents with a chronic disease and/or disability. But when motor competence is inadequate for the type of sport, a feeling of failure could predominate.

While there are many positive reasons for participating in sports or other physical activities for children with a chronic disease and/or disability, attention must be paid to the risk of acute and overuse injuries but also illness. Indeed parents and healthcare providers are wary of injuries due to participation in sports, which could further limit their child’s physical functioning. These worries are confirmed in healthy children. A recent study reported a higher absolute risk of getting injured and a high probability of sustaining the injury when adding physical education hours at school or increasing organized sports outside school (Adirim and Cheng 2003; Trifonov Rexen et al. 2014; World Health Organization 1991). At the same time though, the relative risk of injury seems higher for children with low levels of habitual physical activity (Bloemers et al. 2012). Studies also reported children with disabilities to have a higher risk of injury than children without disabilities, but these studies were limited to just one type of disability, sport, or injury (Sinclair and Xiang 2008). Identifying injury patterns and illness in children with disabilities is important to provide safety in sports activities and to prevent dropout in physical activities and return to an inactive lifestyle (Bloemers et al. 2012; Collard et al. 2009; Webborn et al. 2006).

In summary, children with chronic disease and/or disabilities often show reduced levels of physical activity and fitness and participate less in organized sports compared to their non-disabled peers. The positive effects of sports and daily activities on the psychosocial and physical health, cognition and injury risk as depicted in Fig. 1 already have been reported in a healthy population and disabled adults.

**Fig. 1 Fig1:**
[figure not shown]
Overview of positive relations already established within a population of children and adolescents without a chronic disease and/or disability, and within a population of adults with and without a disability

To date, however, limited evidence exists for these effects of participation in sports by children and adolescents with a physical disability or chronic disease. Therefore, the aim of the HAYS study is to determine both the positive and negative effects of sports related to health outcomes in children with disabilities and chronic childhood onset conditions. Therefore the Health in Adapted Youth Sports (HAYS) Study is designed to determine the positive and negative effects of participation in sports in this specific population.

## Design

The HAYS study will be a cross-sectional study comparing children and adolescents with a physical disability or chronic disease, age 10–19 years, who are actively participating in organized sports to their non-sporting peers. The subjects who participate in sports will be matched on gender, age and diagnosis to their non-sporting peers, Fig. 2.

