### Outcome measures

Table 3 shows an overview of the outcome measures and chosen measurement instruments in this study.

**Table 3 Tab3:** Overview of assessments used instruments, questionnaires and time schedule

Outcome measure	Parameter	Variable	Measurement	Time at location	Time at home
General	Demographics	DOB, Gender, Diagnosis, FMS score, activity level	General questionnaire		5 min
Cardiovascular health	Metabolic parameters	BMI	Height, Weight	5 min	
		Fat Free Mass	BIA		
		Blood pressure	Sphygmomanometer	10 min	
		Arterial stiffness Pulse wave velocity	Arteriograph		
Physical fitness	Aerobic fitness	VO_2peak_ RER Anaerobic threshold	CPET Shuttle run/ride test Bicycle test	30 min	
	Anaerobic fitness	Peak power Mean power	MPST	5 min	
	Muscle strength	Isometric muscle strength Explosive muscle strength	Grip strength Reverse curl Seated push up Standing broad jump or One stroke push	10 min	
	Flexibility		Modified Apley test Modified Thomas test	5 min	
	Agility		10 × 5 meter sprint	5 min	
Physical activity	Intensity	Heart rate	Actiheart	5 min	7 days
	Modality	Type of activity	Activ8 and Activity diary	5 min	7 days
Cognitive functioning	School performance	Educational level	Type of education Recent CITO-score	0 min	
	Attention	Focused attention Sustained attention Strategy Distractibility	Bourdon-Vos Cancellation task Capture task	15 min 5 min	
Injury and illness	Incidence injury and illness	Retrospective 3 months	Online questionnaire		3 min
		Longitudinal 1 year, every 2 weeks	Online questionnaire		
	Classification of injury or illness (if applicable)		Telephone conversation		5 min
Psychosocial health	Self-perception		Self-perception profile for children (SPPC)	10 min	
	Quality of life		Disabkids		10 min
	Self-efficacy		Exercise self-efficacy Scale		2 min
Total time				150 min	28 min

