#### Physical fitness

Physical fitness consists of a combination of aerobic fitness, anaerobic fitness, muscle strength, flexibility and agility. Using the FMS for 500 meters the group of subjects will be divided in two sets depending on their mode of locomotion on this distance: wheelchair users and subjects who are able to walk with or without mobility aids. For these two groups, different testing tools will be used, appropriate for the type of locomotion.

Subsequently, within the group of subjects who are ambulatory different levels of mobility can be identified in order to apply a proper testing protocol, see Table 4.

**Table 4 Tab4:** Level of mobility for identifying testing protocol

Category	Level of mobility
I	Subjects with a very low level of mobility (able to walk <400 m in 6 min)
II	Subjects with a low level of mobility (able to walk > 400 m in 6 min)
III	Subjects with average level of mobility: walking indoors and outdoors and climbing stairs without limitations and able to perform gross motor skills including running and jumping
IV	Subjects with an excellent level of mobility, who are used to run at a speed of 8 km/h during their practicing their sports or during competition

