#### Aerobic fitness

In exercise testing peak, oxygen uptake (VO_2peak_) is considered to be the single best indicator of the cardio-respiratory system, often referred to as aerobic fitness. A cardio-pulmonary exercise testing system, the Cortex Metamax 3X (Samcon bvba, Melle, Belgium), will be used for evaluating the respiratory gasses and VO_2peak_.

Bhambani et al. concluded that maximal exercise testing during the main mode of ambulation elicits the highest oxygen uptake. Therefore the type of sports or daily locomotion determines whether the shuttle run, shuttle ride or a cycling test will be used (Bhambhani et al. 1992).

Children who are able to walk will be tested with an (adapted) shuttle run test (Léger and Lambert 1982; Verschuren et al. 2006). The speed of the shuttle run test will be adjusted based on the results of the muscle power sprint test and the agility test and the level of mobility, see Table 4.

In children with a congenital cardiopulmonary disease a cycling test will be used, because of the monitoring of the heart for safety issues. The cycling test, using the Godfrey protocol (Washington et al. 1994), will also be applied to evaluate the aerobic fitness in children who are active on a bike in sports or daily living. Load depends on height of the child and the expected level of fitness.

A shuttle ride test will be used in children using a wheelchair. Shuttle tests are field tests in which a participant walks or runs between 2 markers. In this case they have to ride a distance of 10 meters in their own wheelchair, if applicable their sports wheelchair, between two cones. The starting speed is 2.0 km/h and the speed is increased with 0.25 km/h every minute. The children have to keep on riding, until they fail to reach the cone two times in a row, despite encouragements. This protocol has been proven valid as a maximal exercise test in youth with CP and spina bifida (Verschuren et al. 2013; Bloemen et al. 2015).

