### Statistical analysis

Data will be checked for normal distribution before applying the right type of parametric or non-parametric tests. First, descriptive statistics will be used to describe the two samples. Independent sample T-tests or appropriate non-parametric tests will be used to to determine the differences between the sport and non-sport group.

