## Discussion

The current paper describes the rationale, design and methods of a cross-sectional study concerning participation in sports focused on children and adolescents with a physical disability or chronic disease.

To our knowledge this is the first study to evaluate this effect of sport participation on physical, social and mental health within this population. The aim is to determine both the positive and negative effects of sports related to health outcomes in children with disabilities and chronic childhood onset conditions. We hypothesize that the group participating in sports regularly will show higher levels of physical activity associated with better health outcomes, a relative lower incidence density, better cognitive functioning and school performance.

New insights gained from this study could stimulate the improvement of facilities for adapted sports by the government. Also children with a chronic disease or physical disability and their caregivers, sport coaches, physical therapists and other interested parties will be more easily convinced of the advantages of sports participation for this population.

Although we carefully chose our study settings according to its population, we are aware of some limitations of the study.

Objective measurements are chosen where possible. To achieve the best results possible, the best fitting testing modality will be chosen for each participant. The testing modality has to mimic the type of sport participated in. In children who do not participate in sport, the most common form of physical activity in daily life will be chosen as an indicator for the test modality. In general, some test modalities have been proven to elicit a higher VO_2_ peak in the same subject (Bhambhani et al. 1992). The test modality could therefore influence the test outcome. To minimalize this bias we will pursue a comparable number of testing modality types in both groups.

In conclusion, this study will provide insight in the effects of sports participation on the health of children and adolescents with a chronic disease or physical disability.

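### Functional mobility is not a matching factor and the stated comparison is unadjusted, so a sport v non-sport difference can partly reflect mobility and should be read as an association

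*Protocol article*

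**What the plan says.** - **Matching (Design):** "The subjects who participate in sports will be matched on gender, age and diagnosis to their non-sporting peers".
- **Analysis (Statistical analysis):** "Independent sample T-tests or appropriate non-parametric tests will be used to to determine the differences between the sport and non-sport group". No covariate or stratum is named, and the test stated does not use the matching.
- **Mobility (Participants; Physical fitness, Table 4):** Walkers and manual wheelchair users are both eligible. On the FMS 500 m item, "the group of subjects will be divided in two sets depending on their mode of locomotion on this distance", and "For these two groups, different testing tools will be used, appropriate for the type of locomotion". Table 4 grades walkers in four levels, from under 400 m in 6 minutes to running at 8 km/h in sport.
- **Choice of aerobic test (Aerobic fitness):** "Therefore the type of sports or daily locomotion determines whether the shuttle run, shuttle ride or a cycling test will be used". Children with congenital cardiopulmonary disease cycle.
- **Data available (Outcome measures, Table 3):** the general questionnaire records "DOB, Gender, Diagnosis, FMS score, activity level".
- **Mitigation (Discussion):** the authors accept that test modality can influence VO2peak and intend to seek similar numbers of each modality in the two groups.
- **Claims:** the Background says that the study is designed to "determine the positive and negative effects of participation in sports in this specific population". The Discussion expects that families and professionals "will be more easily convinced of the advantages of sports participation for this population".

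**The concern.** Matching on diagnosis does not fix mobility. The article itself cites the wheelchair shuttle ride as validated in cerebral palsy and spina bifida. It also takes its VO2peak mean for the sample size from a cerebral palsy study. Two children with the same diagnosis, sex and age can therefore differ widely in mobility.

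Mobility plausibly acts on both sides of the comparison. More mobile children may find sport easier to enter, and they are likely to score higher on VO2peak, power, strength and agility. If the sport group holds more of them, an unadjusted test attributes their advantage to sport. The design is also cross-sectional, so it cannot separate sport improving fitness from fitter children taking up sport. The result could then be presented to families as a benefit of sport when part of it is selection.

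**Working it through.** **1. The plan's own figures (Sample size section).** Mean 42, SD 8.2 ml/kg/min, difference 10 %, alpha 0.05 (two-sided assumed), power 0.80.

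- Target difference = 0.10 × 42 = 4.2 ml/kg/min.
- n per group = 2 × (1.96 + 0.84)² × 8.2² / 4.2² = 60 (61 with the t distribution).
- The plan states 66, which is exact for a difference of 4.0. At 66 per group and 4.2 the power is 0.84. This mismatch errs on the larger side and is not the point here.
- Total: 132 × 1.10 = 145.2, rounded up to the stated 146.

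**2. Standard error of the planned contrast.** SE = 8.2 × √(2/66) = 1.43 ml/kg/min.

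**3. Bias from unbalanced mobility.** Suppose sport makes no true difference. With two mobility classes whose mean VO2peak differs by D, and a between-group difference p in the share of the more mobile class:

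- bias b = p × D
- chance of a significant result = 1 − Φ(1.96 − b/1.43) + Φ(−1.96 − b/1.43)

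The documents give neither D nor p. The assumed ranges are D from 5 to 15 ml/kg/min and p from 10 to 30 points.

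| p | D | b | b / 4.2 | False-positive rate |
|---|---|---|---|---|
| 0.10 | 5 | 0.5 | 12 % | 6 % |
| 0.15 | 10 | 1.5 | 36 % | 18 % |
| 0.20 | 10 | 2.0 | 48 % | 29 % |
| 0.30 | 15 | 4.5 | 107 % | 88 % |

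A smaller imbalance does little harm: at 5 points, gaps of 4 to 16 ml/kg/min give b = 0.2 to 0.8 and a rate of 5 % to 9 %. The SD is held at 8.2 throughout. A wider SD in a mixed-diagnosis sample would lower these rates but leave b unchanged.

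**4. What adjustment costs.** Let R² be the share of VO2peak variance explained by mobility, and r the correlation of mobility with sport group. Approximate n per group for 4.2 = 60 × (1 − R²)/(1 − r²), computed from the unrounded 59.8 and rounded up:

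- R² = 0, r = 0.2: 63
- R² = 0, r = 0.4: 72
- R² = 0.1, r = 0.4: 65
- R² = 0.3, r = 0.4: 50

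Of these, only the second exceeds the planned 66. There mobility explains none of VO2peak, so it would not confound that outcome. Where mobility does explain VO2peak, the gain in precision offsets some or all of the loss.

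**5. Does the modality intention close the gap?**

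- Wheelchair users take the shuttle ride, so similar numbers of each modality would help to balance them against walkers.
- The intention has no rule or tolerance.
- It does not address the four Table 4 levels among walkers.
- In sporting subjects the modality follows the sport played, so it is partly a consequence of the exposure and cannot stand in for FMS.
- It is not carried into the stated test.

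**The case against.** The strongest reply is that the authors saw a related bias and planned for it by balancing modality. That stands in part: the step should be credited, but it is incomplete for the reasons in the last step of the working.

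A second reply is that an article condenses the full protocol, and an analysis plan that is not shown may add covariates. Silence on covariates alone would indeed be no finding. Here, however, a method is stated, it is unadjusted, and the listed matching factors leave mobility out.

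A third reply is that the causal wording is a matter of style. The article calls itself cross-sectional, its methods speak of differences, its hypothesis speaks of association, and a separate controlled trial is to test effectiveness. That makes the rewording easy. But the aim and conclusion still claim effects, and the limitations discussed concern only test modality.

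A reader might also infer more than the documents support:

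- **That mobility decides who plays sport.** No section says so; the influence is plausible only.
- **That mobility alone decides the test.** The aerobic test also depends on the sport played and, for congenital cardiopulmonary disease, on the condition.
- **That jump and push distances are pooled.** The Strength section limits the standing broad jump to walkers and gives wheelchair users the one stroke push. How either is compared is not stated.
- **That the sport group comes from clubs and the other from hospital or rehabilitation.** The Recruitment section gives one list of sources and does not divide it by group.
- **That the false-positive rate is 18 % to 29 %.** This needs an assumed gap of 10 ml/kg/min and 15 to 20 points of imbalance; at the low end of the same range the rate is about 6 %.

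**Conclusion.** The point holds in a limited form. As stated, neither the matching factors nor the analysis controls functional mobility, and the intended balance of test modality is only a partial safeguard. The bias may be negligible or as large as the effect sought: 0.5 to 4.5 ml/kg/min against 4.2, under an assumed gap of 5 to 15 ml/kg/min and an imbalance of 10 to 30 points. The documents do not show which applies. It would be too strong to say that the comparison is invalid or that a false positive is likely. The supportable conclusion is that the stated contrast can show an association, not an effect of sport, and that a less biased analysis is available from data already collected.

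**What to change.** 1. In Statistical analysis, replace the unadjusted comparison with a regression of each outcome on sport group, adjusting for FMS locomotion or mobility level and for gender, age and diagnosis. Adjust for FMS rather than test modality, because modality partly follows from the sport played.
2. Where feasible, add FMS 500 m locomotion (wheelchair v walking) to the matching factors.
3. State that locomotion-specific tests, such as the standing broad jump and the one stroke push, are compared within locomotion group.
4. Word the aim and conclusion as associations with sports participation, and name confounding by mobility and reverse causation as limitations.

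**Cost:** FMS is already recorded, so items 1, 3 and 4 need no new data. Item 2 makes matches harder to fill across many diagnoses; if it proves impracticable, item 1 still adjusts for mobility in the analysis. Adjustment may lose some precision if mobility is strongly related to sport participation. In the scenarios shown, the planned 66 per group suffices except where mobility explains none of VO2peak and r = 0.4, which needs 72.
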